### Study design

2.1 

This is a multicenter cluster randomized controlled trial conducted by the Chinese Critical Care Nutrition Trials Group (ChiCTR2400081581^1^; NCT06827275^2^). The trial protocol was developed in accordance with the Standard Protocol Items: Recommendations for Interventional Trials (SPIRIT) statement (11). The final version of the plan is 5.0, with the date being 16 December 2024.

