### Sample size calculation

2.3 

Sample size calculation was performed using PASS software. The primary clinical outcome was the difference in the incidence of FI between the two groups. Based on previous studies, the incidence of FI among critically ill patients in the control group was assumed to be 0.5. According to the clinical decision curve analysis from the predictive model for FI (NOFI) (10), the net benefit at a threshold probability of approximately 50% was 0.257, indicating that around 25.7 patients out of every 100 would benefit from the intervention. Therefore, it was assumed that the mNEED protocol (intervention group) would reduce the incidence of FI by 25%, resulting in an expected FI rate of 0.375 in the intervention group [0.5 × (1–0.25) = 0.375]. We set the intraclass correlation coefficient (ICC) to 0.10 by analogy to the NEED trial (4), a total of 45 clusters per group were planned, with an ICC of 0.1. Using a two-sided alpha of 0.05 and a statistical power of 90% (1–β = 0.9), the required number of participants per cluster was calculated to be 25. Thus, the total sample size was 45 clusters × 25 participants × 2 groups = 2,250 participants. We pre-specified ICC sensitivity analyses, which indicated that the planned configuration is robust to plausible ICC and cluster-size variability; detailed results are provided in Supplementary Tables 3, 4.

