#### Intervention fidelity, contamination, and exposure

2.6.6 

Fidelity: Using the electronic feeding logs and CRFs, we will quantify protocol fidelity in the mNEED arm as the proportion of patients who completed every protocol-mandated EN dose adjustment at each scheduled assessment (per protocol rules). This will be summarized at patient and ICU (cluster) levels.

Contamination (control arm): Each control ICU will be contacted to confirm whether NOFI (the FI prediction model) was used to guide EN decisions. Any reported use of NOFI to guide EN in the control arm will be recorded as intervention contamination for that ICU.

Exposure metrics. To contextualize delivery of nutrition support, we will report: (i) time to EN initiation from ICU admission; and (ii) duration (days) under protocol-managed nutrition. These process measures are not clinical endpoints; they will be summarized descriptively and compared between arms.

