#### Data analysis

2.7.1 

All statistical analyses will be conducted in accordance with a pre-specified statistical analysis plan. The primary analysis will follow the intention-to-treat (ITT) principle, with adjustment for clustering. The primary outcome (FI, binary) will be analyzed using a generalized linear mixed model (GLMM, logit link) with a random intercept for ICU/cluster and fixed effects for treatment and the pre-specified covariates (APACHE II score, AGI grade, primary diagnosis). To guard against model mis-specification and unequal cluster sizes, cluster-robust (sandwich) standard errors will be used for inference with between-cluster degrees of freedom; if convergence or small-sample issues arise, a wild cluster bootstrap-t procedure will be applied as a pre-specified fallback. Operationally, the full analysis set (FAS) will be used, defined as all randomized patients who have at least one valid post-randomization assessment of the primary outcome. The PPS, defined as patients who received protocolized EN for at least 48 h, will be used for sensitivity analyses.

Binary secondary outcomes (e.g., achievement of nutritional targets by day 7) will be analyzed analogously with GLMM (logit); continuous outcomes will use linear mixed models with a cluster random intercept and Kenward–Roger degrees-of-freedom adjustment. In addition, the EFI will be applied as a prespecified sensitivity analysis of the primary outcome to assess the robustness of the findings.

Continuous variables will be summarized as mean ± standard deviation if normally distributed, or as median and interquartile range (IQR, P25–P75) if not normally distributed. Between-group differences in continuous variables will be tested using the independent samples *t*-test for normally distributed data or the Mann–Whitney *U*-test for non-normally distributed data. Categorical variables will be compared using the Chi-square test.

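### Two sentences in the Data analysis section prescribe patient-level t, Mann-Whitney and chi-square tests without limiting their scope or allowing for ICU clustering

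*Protocol article*

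**What the plan says.** Section 2.1 states the design: "This is a multicenter cluster randomized controlled trial". Section 2.4.1 confirms that ICUs were the units allocated, 54 to each arm.

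Section 2.7.1 first assigns clustered models to the outcomes. The primary outcome has a logistic mixed model with an ICU random intercept and cluster-robust standard errors. Binary secondary outcomes are handled in the same way. For the rest, "continuous outcomes will use linear mixed models with a cluster random intercept", with Kenward-Roger degrees of freedom.

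The third paragraph of that section opens with the rule for descriptive summaries (mean and SD, or median and IQR). It then adds two test sentences. The first is "Between-group differences in continuous variables will be tested using the independent samples" t-test, or the Mann-Whitney test if the data are not normal. The second is "Categorical variables will be compared using the Chi-square test". Neither names a set of variables or mentions the ICU.

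The section closes by taking the p-values for clinical secondary endpoints from the specified models. It makes process outcomes, listed in brackets as fidelity, exposure and contamination, descriptive with 95% CIs and without hypothesis tests. Section 2.6.6, on its two exposure metrics (time to EN initiation and days under protocol-managed nutrition), says "they will be summarized descriptively and compared between arms".

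**The concern.** The three named tests treat patients as independent. Patients in one ICU share staff, habits and case mix, and the ICU is what was randomised. The true variance of a difference between arms is therefore larger than these tests assume, and their p-values are too small.

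Three places are exposed:

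- **Continuous outcomes.** They already have a linear mixed model. The two sentences add a second test with a different standard error. The temptation is greatest for outcomes that are usually skewed, such as ICU length of stay and ventilator-free days, because the Mann-Whitney test is the only method section 2.7.1 names for non-normal data.
- **Baseline variables.** Unclustered tests would flag imbalances that are only ICU-to-ICU variation.
- **Process measures in section 2.6.3 outside the bracketed list.** Examples are energy and protein delivered and the percentage fed within 24 h. They show whether the arms really differed in feeding, so a false difference would colour how the feeding-intolerance result is read.

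**Working it through.** **Inputs.** Section 2.3 gives the planning values: "the incidence of FI among critically ill patients in the control group was assumed to be 0.5"; "resulting in an expected FI rate of 0.375 in the intervention group"; "We set the intraclass correlation coefficient (ICC) to 0.10 by analogy to the NEED trial". It also gives 45 clusters per arm, 25 patients per cluster, two-sided alpha 0.05, 90% power and a total of 2,250. Section 2.4.1 gives 108 ICUs. If the total stays at 2,250 (an assumption), the mean cluster size is 2,250/108 = 20.8.

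**Step 1: the plan's own figure.** Comparing 0.50 with 0.375 at 90% power needs n = 329 per arm under individual randomisation. With K = 45 clusters per arm and ICC ρ = 0.10, solve K·m = n·[1 + (m − 1)ρ] for the cluster size m:

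m = n(1 − ρ)/(K − nρ) = 329 × 0.9/(45 − 32.9) = 296.1/12.1 = 24.5, rounded up to 25.

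The design effect at m = 25 is 1 + 24 × 0.10 = 3.40, and 329 × 3.40 = 1,119 against the planned 1,125 per arm. Power is 90.2%. The plan's sample size reproduces, so the same design effect can be applied to the unclustered tests.

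**Step 2: actual false-positive rate of an unclustered test.** With DE = 1 + (m − 1)ρ, the test understates the standard error by √DE, so the actual rate is 2·[1 − Φ(1.96/√DE)]. For ρ = 0.10 and m = 25, √3.40 = 1.84, 1.96/1.84 = 1.06, and the rate is 28.8%.

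| ICC | DE, m = 25 | Rate, m = 25 | DE, m = 20.8 | Rate, m = 20.8 |
|---|---|---|---|---|
| 0.01 | 1.24 | 7.8% | 1.20 | 7.3% |
| 0.02 | 1.48 | 10.7% | 1.40 | 9.7% |
| 0.05 | 2.20 | 18.6% | 1.99 | 16.5% |
| 0.10 | 3.40 | 28.8% | 2.98 | 25.6% |

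**Step 3: simulation under no effect, ICC 0.10** (5,000 trials; 3,000 for Mann-Whitney).

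| Test | 45 ICUs of 25 per arm | 54 ICUs of 20 or 21 per arm |
|---|---|---|
| t-test | 28.6% | 25.0% |
| Mann-Whitney | 28.7% | 25.0% |
| Chi-square | 29.2% | 25.1% |
| t-test on ICU means | 5.1% | 4.5% |

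The formula holds for all three named tests, and a simple ICU-level analysis restores the nominal level. Unequal cluster sizes would raise the unclustered rates further.

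**Step 4: where the two sentences can apply.**

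- Primary outcome: clustered model specified; not affected.
- Secondary outcomes: clustered models specified, and the p-values for the false-discovery-rate procedure come from them. The two sentences add a competing test on their face but do not feed that procedure.
- Exposure metrics in section 2.6.6: section 2.7.1 rules out testing, while section 2.6.6 speaks of comparison without naming a method. The wording does not match.
- Other process measures in section 2.6.3: not clearly inside the bracketed list, so the two sentences can be read onto them.
- Baseline variables: no other rule is given, so the two sentences apply.

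**The case against.** The strongest reply is that the paragraph begins with summary statistics and reads as stock wording for descriptive tables. The inference that matters is clustered throughout: even the unadjusted sensitivity analysis keeps the ICU random intercept. Baseline tests cannot change the primary model, because its covariates are fixed in advance and kept whatever their significance. The bracketed list of process outcomes may be meant to cover all of section 2.6.3. The ICC of 0.10 was set for feeding intolerance, and the article gives none for baseline variables or delivered nutrition.

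Most of this stands, and it limits the point. A reader might infer that the trial's between-group testing as a whole runs at a 26-29% false-positive rate. The documents do not support that, because the rate belongs to no planned primary or secondary inference. A reader might also infer that the unclustered tests are the only ones named for time to EN initiation. That fails too, since it is an exposure metric and section 2.7.1 rules out testing it. Nor does the comparison wording in section 2.6.6 extend to energy and protein, which are listed in section 2.6.3.

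What the reply does not remove is the text itself. The sentences carry no limit to descriptive or baseline tables, and an unclustered test would be wrong there as well.

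**Conclusion.** The point holds as a moderate defect: a stated testing rule with no scope that gives wrong p-values wherever it is followed in this design. Its reach is baseline comparisons, process measures not clearly covered by the no-testing rule, and any continuous outcome for which an analyst prefers the simple test to the mixed model. The primary analysis and the model-based secondary analyses are sound in this respect.

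The inflation is small if a variable barely clusters and severe at the value the plan uses for feeding intolerance. Two assumptions carry the range: cluster sizes of 20.8 to 25, the lower of which keeps 2,250 patients across 108 ICUs, and the transfer of an ICC between 0.01 and 0.10 to variables for which the article gives no figure.

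**What to change.** 1. Delete the two test sentences from section 2.7.1 and keep the sentence on descriptive summaries.
2. Present baseline characteristics by arm without p-values.
3. State that every between-arm estimate or confidence interval, including those for process measures, comes from a model with an ICU random intercept or from ICU-level summaries.
4. In section 2.6.6, replace the comparison wording with cluster-adjusted estimates and 95% CIs, so that it agrees with the no-testing rule in section 2.7.1.

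The cost is a few lines of text. Nothing changes in sample size, data collection or conduct. The change should be made before the data are analysed, so that the choice between two tests cannot depend on the results.

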#### Secondary outcome definition and measures

2.6.2 

Achievement of nutritional targets: Receiving at least 80% of the estimated nutritional goals by day 7 after ICU admission(defined as energy intake ≥ 25 kcal/kg/day and protein intake ≥ 1.3 g/kg/day)28-day mortality: Assessed on day 28 after ICU admission90-day mortality: Assessed on day 90 after ICU admissionHealth-related quality of life (HRQoL) measured by SF-36 (Short Form-36 Health Survey): Assessed on days 28 and 90 after ICU admissionHealth-related quality of life measured by EQ-5D-5L (EuroQol 5 Dimensions 5 Levels): Assessed on days 28 and 90 after ICU admissionDiaphragm thickness: Measured on day 7 after ICU admissionQuadriceps muscle thickness: Measured on day 7 after ICU admissionRectus femoris cross-sectional area: Measured on day 7 after ICU admissionUpper limb muscle thickness: Measured on day 7 after ICU admissionNew infections in the ICU: Defined as infections newly acquired ≥ 48 hours after ICU admissionICU length of stayVentilator-free days: Ventilator-free days within 28 days in the ICU

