Sensitivity analyses will include: (i) an unadjusted GLMM (treatment + random intercept only); (ii) a covariate-enriched GLMM that adds baseline mechanical ventilation and sepsis (yes/no; protocol-defined) on top of the pre-specified covariates (APACHE II score, AGI grade, primary diagnosis); and (iii) aFI. All covariates are pre-specified and retained regardless of statistical significance. We will report adjusted odds ratios (95% CIs) for binary endpoints (with marginal risk differences via standardization as supportive estimates). The primary endpoint will be tested at two-sided α = 0.05 without multiplicity adjustment. For prespecified clinical secondary endpoints, we will control the false discovery rate at *q* = 0.05 using the Benjamini–Hochberg procedure (two-sided *p*-values from the specified models). Process outcomes (fidelity, exposure, contamination) are exploratory and will be summarized descriptively with 95% CIs; no hypothesis testing or multiplicity adjustment will be applied to these measures. All analyses will be performed using SAS software version 9.4^®^ (SAS Institute Inc., Cary, NC, United States).

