#### Confidentiality and data security

2.7.3 

All data collected from participating centers will be stored in a secure web-based database. Except for the data administrator (the designated research lead at the coordinating center), no other individual will have the authority to modify, alter, or export patient data or information. Strict measures will be taken to ensure the confidentiality and security of all patient information. An independent Data and Safety Monitoring Board (DSMB)—separate from the sponsor, investigators, and coordinating center—will oversee participant safety and trial conduct under a written charter. An independent statistician will prepare unblinded safety summaries for the DSMB at prespecified intervals; the investigative team will remain blinded. The DSMB may issue recommendations (continue, modify, pause, or terminate) based on predefined safety considerations. Strict measures are in place to ensure confidentiality and data security throughout the study.

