## Discussion

3 

Developing objective, guideline-based feeding protocols may improve outcomes in critically ill patients. Two of the largest cluster-randomized controlled trials to date have investigated this approach—one conducted by Doig et al. across 27 ICUs in Australia and New Zealand (3), and the other by Ke et al. across 97 ICUs in China (4). Unfortunately, neither feeding protocol resulted in improved clinical outcomes for critically ill patients. This raises critical questions: Is the impact of nutritional interventions inherently limited, or did the implemented protocols fail to provide real benefit to patients? The reasons behind these negative results remain unclear.

Upon reviewing the data from both trials, we observed that the intervention protocols did not effectively reduce the incidence of FI compared to standard care. The association between FI and poor clinical outcomes in critically ill patients has been well documented in multiple studies (15, 16). This led us to a bold hypothesis: feeding strategies may influence clinical outcomes by reducing FI, suggesting that FI could be a potential mediator between nutritional intervention and patient prognosis.

Unlike the two previous cluster-randomized controlled trials, our study did not adopt mortality as the primary endpoint. Nutritional interventions represent only one component of the overall management of critically ill patients, and directly reducing mortality through nutritional strategies alone appears challenging. The prior two trials did not demonstrate a mortality benefit, nor did they show a reduction in the incidence of FI. Therefore, in the present study we selected FI as the primary endpoint, as it is one of the most clinically relevant indicators of nutritional implementation and has been shown to be associated with patient outcomes (15). Although we do not think the mortality of the mNEED group will be lower, we expect it to at least reduce the occurrence of FI, which might also be beneficial.

A recently proposed concept further supports this hypothesis: in early nutrition, “less is more (17, 18).” Full-dose early nutrition may not benefit, and could even harm, critically ill patients by contributing to overfeeding (18). Therefore, a more promising approach may be to minimize FI while maintaining a gradual feeding progression.

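### The false-discovery-rate rule for the secondary endpoints has no exception for harm, so the formal label on an excess of deaths or infections depends on unrelated endpoints

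*Protocol article*

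**What the plan says.** Section 2.7.1 (Data analysis) sets the multiplicity rule: "For prespecified clinical secondary endpoints, we will control the false discovery rate at" a level q of "0.05 using the Benjamini–Hochberg procedure", with two-sided p-values from the specified models. The primary endpoint is tested at 0.05 without adjustment. For process outcomes, "no hypothesis testing or multiplicity adjustment will be applied to these measures". No other measure is placed outside the rule.

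Section 2.6.2 lists 12 secondary outcomes: nutritional targets, 28-day mortality, 90-day mortality, SF-36, EQ-5D-5L, four muscle-ultrasound measures, new ICU infections, ICU length of stay and ventilator-free days. The mortality entry reads "28-day mortality: Assessed on day 28 after ICU admission", with a matching entry for day 90. The article does not spell out which of the 12 are the clinical endpoints of the rule, but on any ordinary reading mortality and new infections are.

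Three other statements bear on the point. Section 2.7.1 also says "We will report adjusted odds ratios (95% CIs) for binary endpoints", with marginal risk differences as supportive estimates. Section 2.7.3 sets up an independent board: "The DSMB may issue recommendations (continue, modify, pause, or terminate) based on predefined safety considerations". The Discussion says "Although we do not think the mortality of the mNEED group will be lower".

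**The concern.** Multiplicity control on secondary endpoints protects against false claims of benefit. Applied to a harmful difference, it mainly raises the chance of not declaring it. A two-sided Benjamini-Hochberg rule treats both directions alike.

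This matters here because the Discussion does not expect lower mortality under mNEED. A large part of what the mortality comparison can tell the reader is therefore whether the protocol does harm. The Discussion also reports that two earlier feeding-protocol trials did not improve clinical outcomes, so a secondary family that is mostly null is plausible, and that is where the rule is strictest.

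If feeding intolerance falls and deaths rise, the declared rule could label the deaths not significant because muscle thickness and quality-of-life scores in the same family did not differ. The same data could lead to the opposite label had those endpoints differed.

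**Working it through.** **Arm size.** The plan states no Benjamini-Hochberg threshold, so its own figure to reproduce is the sample size (section 2.3). For 0.50 v 0.375, two-sided alpha 0.05 and 90% power, individual randomisation needs n = 329 per arm. With K = 45 clusters per arm and ICC 0.10, patients per cluster = n(1 − ICC)/(K − n × ICC) = 329 × 0.9/(45 − 32.9) = 24.5, rounded up to 25. This matches the plan and gives 45 × 25 = 1,125 per arm.

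**Cut-offs.** With m tests ordered by p-value, the cut-off at rank i is i × 0.05/m. Benjamini-Hochberg finds the highest rank whose p-value meets its cut-off and rejects everything up to it.
- Mortality the only signal: 0.05/12 = 0.0042. If SF-36 and EQ-5D-5L each count at days 28 and 90, m = 14 and it is 0.05/14 = 0.0036.
- Both mortality endpoints moving together: 2 × 0.05/12 = 0.0083.
- All 12 meeting the last rank: 0.05.

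**Effect on detection.** Assumptions, none of them from the documents: deaths 20% v 26%; mortality ICC 0.01, 0.05 or 0.10; the two mortality endpoints shifted equally, with correlation 0.85 between their test statistics; the other ten statistics independent. Effective n per arm = 1,125/(1 + 24 × ICC). The expected statistic is z = 0.06/√(2 × 0.23 × 0.77/n_eff).

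The full Benjamini-Hochberg procedure (m = 12, q = 0.05) was simulated with 400,000 draws per setting, once with the other ten endpoints null and once with three of them strongly positive (mean z = 3.5). Probability that 28-day mortality is flagged:

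| ICC | n_eff | z | Unadjusted 0.05 | BH, other ten null | BH, three others positive |
|---|---|---|---|---|---|
| 0.01 | 1,125/1.24 = 907 | 3.04 | 86% | 63% | 75% |
| 0.05 | 1,125/2.2 = 511 | 2.28 | 63% | 33% | 46% |
| 0.10 | 1,125/3.4 = 331 | 1.83 | 45% | 19% | 29% |

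The loss is 23, 30 and 26 percentage points with the other ten null, and 11, 17 and 16 points with three others positive. The last two columns also show the dependence on unrelated endpoints: at ICC 0.05 the same excess of deaths is flagged 33% or 46% of the time according to how three other outcomes behave.

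**The case against.** The strongest reply is that the excess would be seen anyway. The odds ratios with 95% confidence intervals and the risk differences for binary endpoints are not said to be adjusted or withheld when the rule is not met, and the DSMB acts on its own safety considerations. This stands. A reader might infer that deaths must pass the adjusted threshold before they count at all; the documents do not say so, since the rule governs only the formal declaration. But the DSMB oversees the trial and does not set how the final report labels mortality. An interval excluding no effect beside a not-significant label leaves two readings, with no stated rule for which prevails on harm.

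A reader might also take 0.0042 as the hurdle mortality always faces. It is only the floor. Power at a fixed 0.0042 (28% at ICC 0.05) is Bonferroni power, whereas the planned procedure gives 33% even with the other ten null. Nor is there one fixed route by which other endpoints help. A mortality p of 0.022 is rejected if six others stand at 0.028 and five at 0.5, because the rank-7 cut-off is 7 × 0.05/12 = 0.0292.

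A third tempting inference is that mNEED feeds more slowly than this trial's control arm. Section 2.4.3.1 describes reductions relative to the original NEED protocol. The control arm has no specified feeding protocol and is also held to no more than 70% of energy expenditure in the first three days (2.4.3.2). Slower feeding than control is possible but not stated, and the point does not need it.

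Finally, the article also treats mortality as something that might improve: the Introduction hopes for better prognosis, and the strengths section sees feeding intolerance as a pathway to mortality. Keeping mortality in the family for claims of benefit is therefore coherent. The full analysis plan is not shown and may say more about harm, but the rule as published carries no exception.

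**Conclusion.** The point holds in a limited form. As written, the two-sided false-discovery-rate rule covers 28-day mortality, 90-day mortality and new infections in both directions, so it makes an excess of deaths or infections harder to declare and ties that label to unrelated endpoints. Under the assumptions above, the loss in the chance of flagging 28-day mortality is about 11 to 30 percentage points.

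That size rests on assumed death rates, an assumed ICC and correlation, and a family of 12 read from section 2.6.2. A larger family, for example with several SF-36 scores, would lower the floor; a smaller one would raise it. The defect concerns how the final report labels harm. It does not hide harm, and it does not affect the primary analysis or the sample size.

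**What to change.** Add to section 2.7.1, and to the analysis plan, that Benjamini-Hochberg control applies to claims of benefit only. State that 28-day mortality, 90-day mortality and new ICU infections are also read as safety outcomes from the unadjusted (not multiplicity-corrected) odds ratio and risk difference with 95% confidence intervals. An interval that excludes no effect in the harmful direction is then reported as a harm signal whatever the result for feeding intolerance. Listing the endpoints that form the family would fix m at the same time.

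This is a change of wording, with no new data and no effect on the sample size or on the protection of benefit claims. The downside is a slightly higher chance of a false harm signal. With no true effect, each 95% interval errs in the harmful direction 2.5% of the time, so three endpoints give at most 3 × 2.5% = 7.5%, and less in practice because the two mortality endpoints share deaths.
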